Based on the proven health-enhancing effects of PA on LBP and wellbeing, exercise therapy is an integral part of musculoskeletal rehabilitation in LBP patients [16] and therefore widely recommended as a successful therapy for that patient group [13, 17]. Nevertheless, only a few patients integrate health-enhancing physical activity and/or sport activities in their lifestyle. Based on the bio-psycho-social ICF model of functioning, disability and health [18], exercise therapy aims not only at improving body functions but also at improving participation by means of physiotherapy, therapeutic exercise, strengthening exercises, functional task-oriented training and aerobic training [19]. With regard to sustainability of exercise therapy in rehabilitation, its superior aim is to lead patients to an active lifestyle [12, 20]. Athough many studies have shown the effectiveness of exercise therapy in LBP patients, evidence on sustainability is lacking [21]. In consequence, adherence to self-directed exercise and implementing a health-enhancing PA in daily routine after rehabilitation is a common problem for patients [22]. Focussing PA behavior after rehabilitation, there only is evidence on short-term effects. In this context, barriers frequently mentioned are interface problems (e.g. the patients’ not knowing where to train) and lack of patient-oriented knowledge (e.g., being afraid of making mistakes by being physically active). In consequence, support in PA behavior at home is considered to be important [23].

This paper describes the *Movement Coaching* trial, evaluating a multilevel approach promoting PA. The primary research question of this study is:

Does *Movement Coaching* lead to a higher level of PA in chronic LBP patients compared to a control group?

Related to the primary research question, the following hypotheses were developed:The intervention group *(Movement Coaching)* shows 360 MET-min per week more PA than the control group at six months (resp. twelve months) after inpatient rehabilitation.The intervention group *(Movement Coaching)* shows a higher level of leisure time PA than the control group at six months (resp. twelve months) after inpatient rehabilitation.The intervention group *(Movement Coaching)* shows a higher level of transport PA than the control group at six months (resp. twelve months) after inpatient rehabilitation.

Additionally, the following secondary research question is evaluated by an explanatory approach:

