### Measurements

Data are collected by questionnaire at each of the three measurement points. The main outcome PA was operationalised by the Global Physical Activity Questionnaire (GPAQ) [30, 31]. GPAQ measures prevalence of physical inactivity as well as frequency per week and duration of PA differentiated in three domains, respectively life areas: work (paid and unpaid), transport (e.g., walking and cycling to get to and from places) and leisure time. For each domain, PA conducted for at least 10 minutes continuously during a usual week is assessed. Thereby, work and leisure time PA is measured intensity-specific, which allows to distinguish information on vigorous and moderate PA. Concurrent validity of GPAQ was assessed by comparison with International Physical Activity Questionnaire (IPAQ), a previously validated and accepted measure of physical activity. Thereby, GPAQ showed a moderate to strong positive relationship (concurrent validity: Spearman’s rho 0.45 – 0.65). Reliability was of moderate to substantial strength (kappa 0.67 to 0.73; Spearman’s rho 0.67 to 0.81) [31].

Additionally, a subgroup of 20 patients will receive an accelerometer for the measurement of objective PA at T2 (6 months follow-up). Objective PA will be measured through ActiGraph GT3X tri-axial accelerometers. Participants will be instructed to wear the monitor on a belt around their waist for seven days except during sleeping, showering or swimming. We offer financial incentives to complete questionnaires or to wear accelerometers. Table 2 gives a summary of all measures that will be collected.

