### Sample size

The power calculation is based on the main hypothesis (hypothesis 1). Therefore it is assumed that the intervention group *(Movement Coaching)* shows 90 min per week more PA than the control group. The assumption is based on the estimation of a baseline PA level of 60 min per week in average. On the one hand, an increase of 90 min per week is considered realistic from a practical point of view, on the other hand it is considered a relevant effect as the achieved 150 min per week (assumption: baseline PA = 60 min per week + increase by Movement Coaching = 90 min per week) would go in line with the WHO recommendations on PA [15]. In this current RCT study, 264 participants (132 per group) were calculated to be necessary to detect the assumed relevant difference of 90 min moderate PA per week (~360 MET-min) between the two groups at a two-sided significance level of 0.05 (power 0.8). Anticipating on maximum loss to follow-up of 35% and using a non-parametric statistic test (+5%) the calculated target sample size is 370 patients.

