### Statistical analysis

Descriptive statistics will be used to describe the main characteristics of the study population.

The primary analysis will be performed according to the per protocol principle. In addition, an intention-to-treat analysis will be performed. Differences between the intervention group (Movement Coaching) and the control group will be evaluated by Mann-Whithney-U Test at six month (T2) and twelve month follow-up. For all analyses, a two-tailed significance level of p <0.05 is considered to be statistically significant. All analyses will be carried out with IBM SPSS Statistics 21.0.

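### The stated Mann-Whitney comparison leaves out the T1 GPAQ value and gives no difference in MET-min; a baseline-adjusted rank test with an adjusted MET-min estimate would be a low-cost improvement

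*Protocol article*

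**What the plan says.** - **Test.** Under Statistical analysis, differences between the two groups "will be evaluated by Mann-Whithney-U Test at six month (T2) and twelve month follow-up". The section names no covariate, change score, effect estimate or confidence interval. It makes the per-protocol analysis primary and adds an intention-to-treat analysis.
- **Hypothesis.** In the Background, hypothesis 1 is worded as an amount: the intervention group "shows 360 MET-min per week more PA than the control group at six months (resp. twelve months) after inpatient rehabilitation".
- **Sample size.** This section calls hypothesis 1 the main hypothesis and plans to "detect the assumed relevant difference of 90 min moderate PA per week (~360 MET-min) between the two groups"; "264 participants (132 per group) were calculated to be necessary". It then allows for up to 35% loss to follow-up and adds 5% for a non-parametric test, so the rank test was chosen deliberately.
- **Baseline.** Under Measurements, "Data are collected by questionnaire at each of the three measurement points". Table 2 lists GPAQ, the primary outcome instrument, at T1, T2 and T3.

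**The concern.** Two things do not fit together.

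First, the same questionnaire is completed before the intervention, and its value is normally the best available predictor of the follow-up value. A two-sample Mann-Whitney test at T2 or T3 cannot use it. If the groups differ by chance in activity at T1, the stated test does not correct for that. The point carries some weight here because the primary set is per protocol and up to 35% of patients may be lost. The groups analysed need not be the groups randomised.

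Second, the main hypothesis and the planning are in MET-min per week, but the test compares rank order. A reader of the results would learn whether the groups differ, but not by how many MET-min, nor how that compares with the 360 the trial calls relevant.

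**Working it through.** **1. The plan's own figure.** The article gives no SD, so 132 per group can be neither confirmed nor refuted; it can only be solved backwards. With n per arm = 2(z₀.₉₇₅ + z₀.₈₀)²/d², d = 0.345 gives 2 × (1.960 + 0.842)²/0.345² ≈ 132. The implied SD is 360/0.345 ≈ 1,044 MET-min. The t-test version gives d = 0.346 and SD ≈ 1,040.

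**2. Inputs for the power check.**
- From the article: 132 per arm, two-sided 0.05, difference 360.
- Back-solved: SD 1,040.
- Assumed: lognormal data; control mean 1,000; a proportional effect of 36% (0.36 × 1,000 = 360); log-scale correlation r between T1 and follow-up of 0.2, 0.3 or 0.5.

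The log-scale SD is √ln(1 + 1.04²) = 0.856, and the log-scale effect is ln(1.36)/0.856 = 0.3075/0.856 = 0.359. Given a coefficient of variation of 1.04 and a ratio of 1.36, these rank-test results do not depend on the mean of 1,000.

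**3. Unadjusted rank test.** Its efficiency on log-normal data is 3/π = 0.955. The expected z is 0.359 × √(132 × 0.955/2) = 2.85, so power = Φ(2.85 − 1.96) = Φ(0.89) ≈ 0.81. Simulation gives about 0.80.

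**4. Rank test adjusted for T1.** In rank ANCOVA, the rank of the follow-up value is regressed on arm and the rank of T1 GPAQ. The rank correlation is ρ = (6/π) arcsin(r/2), and z is divided by √(1 − ρ²).

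| r (log scale) | ρ | z | Power, formula | Power, simulated |
|---|---|---|---|---|
| none used | – | 2.85 | 0.81 | about 0.80 |
| 0.2 | 0.191 | 2.90 | 0.83 | 0.82 |
| 0.3 | 0.288 | 2.98 | 0.85 | 0.84 |
| 0.5 | 0.483 | 3.26 | 0.90 | 0.90 |

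In simulation, the adjusted rank test kept its type I error at about 5%. It matched or beat Mann-Whitney in every effect shape tried.

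**5. Does the p-value say anything about 360?** Take two lognormal arms with the same median of 600 and log-scale SDs of 1 and 1.273. The means are 600 × exp(0.5) = 989 and 600 × exp(1.273²/2) = 1,349, which differ by 360. Mann-Whitney rejected in 5.3% of runs, which is its error level. Conversely, a uniform shift of only 180 on data with mean 1,000 and SD 1,040 was rejected in about 80% of runs. Both cases are constructed and are not forecasts. They show only that the test result cannot be read as a statement about 360 MET-min.

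**6. Would a raw-scale mean model be a better primary test?** Simulated power on the same lognormal data, 132 per arm, r = 0.3, with robust (HC3) errors for the ANCOVA:

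| Effect | Mann-Whitney | Raw-scale ANCOVA |
|---|---|---|
| +36% for everyone | 0.80 | 0.70 |
| +180 for everyone | 0.81 | 0.34 |
| Mean +360, all of it in 10% of patients | 0.26 | 0.64 |

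The ranking depends on the shape of the effect, which the article does not give.

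**The case against.** The strongest defence has four parts.

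- **The unadjusted test is valid.** Randomisation protects its error rate whether or not T1 is used. This stands. It is less complete for a per-protocol set with substantial loss, and adjusting for T1 GPAQ would correct only imbalance in that one variable.
- **The 360 is the planning difference.** The Sample size section calls it the assumed relevant difference to be detected, with a two-sided test. On that reading, hypothesis 1 is tested against no difference, and a rank test can do that. This largely stands. A reader might infer from the wording of hypothesis 1 that the trial cannot answer its main question; the documents do not support that. What remains is that no estimate is stated to set against 360.
- **A rank test suits skewed activity data.** This stands. A reader might infer that power is being squandered and that ANCOVA on raw MET-min should replace the rank test. The last table under the working shows that this swap would often lower power. Gains worked out from normal theory do not carry over to it.
- **An article leaves adjusted analyses and intervals to the full plan.** This stands in part. A fuller plan may contain them, and that caps the weight of the point. The article nevertheless fixes the test for the main hypothesis, and that test takes no covariate.

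A reader might also add that the trial is already below 80% power. That is a separate question about the allowance for loss. It rests on an SD the article does not state, and 412 patients were recruited against a target of 370. It is not relied on here.

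**Conclusion.** The point holds as an improvement to the plan. The stated comparison does not use the T1 value of the primary outcome and yields no MET-min difference, although the main hypothesis and the sample size are in MET-min. The cost is precision, protection against baseline imbalance and an interpretable effect size. It is not a biased or invalid test.

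On the assumptions shown, adjusting the rank test adds about 2, 4 or 10 percentage points of power at r = 0.2, 0.3 or 0.5. The size rests on an assumed correlation, lognormal data without zeros, a proportional effect and a back-solved SD. The article's only baseline figure is 60 minutes per week, about 240 MET-min at its own conversion (360/90 = 4 per minute). The mean of 1,000 is therefore illustrative, and so are the raw-scale comparisons that use it. If the correlation is weak, the gain in power is small. The case for an estimate with an interval does not depend on it.

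**What to change.** - **Primary test.** Keep it rank-based at T2 and T3, but adjust for T1 GPAQ, for example by rank ANCOVA.
- **Estimate.** Report alongside it a baseline-adjusted difference in MET-min per week at T2 and T3, with a robust or bootstrap 95% confidence interval.
- **Hypothesis 1.** Word the test as a difference from zero, and name 360 MET-min per week as the benchmark of relevance against which the interval is read.
- **Analysis sets.** Apply the same specification to the per-protocol and intention-to-treat analyses.

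The cost is a change of analysis wording and slightly more analysis work. No new measurement is needed, since GPAQ is already scheduled at all three points. The article expects T3 to be complete in April 2015, so the change could be recorded before the final analysis. The main downside is that intervals for means of skewed data can be wide. That is one reason for keeping the rank-based test primary and not making a raw-scale mean model the only primary analysis.

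### The main hypothesis is tested at both six and twelve months, each at 0.05, but the sample size budgets for one 0.05 test and no primary time point or success rule is stated

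*Protocol article*

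**What the plan says.** The Background section introduces the hypotheses with "Related to the primary research question, the following hypotheses were developed". Hypothesis 1 is that the intervention group "shows 360 MET-min per week more PA than the control group at six months (resp. twelve months) after inpatient rehabilitation". Hypotheses 2 and 3 concern leisure-time and transport activity, with the same pair of time points.

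The Sample size section gives hypothesis 1 a special rank: "The power calculation is based on the main hypothesis (hypothesis 1"). It arrives at 264 evaluable patients (132 per group) for a difference of about 360 MET-min per week, "at a two-sided significance level of 0.05 (power 0.8"). It does not say whether this refers to six or twelve months.

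The Statistical analysis section says that group differences "will be evaluated by Mann-Whithney-U Test at six month (T2) and twelve month follow-up". Its only decision rule is "For all analyses, a two-tailed significance level of p <0.05 is considered to be statistically significant".

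The abstract, the Study design section and the table of measures name physical activity by GPAQ as the primary outcome, or list both follow-ups. None of them names a primary time point. The article contains no rule that both time points must succeed, no split of the significance level and no testing sequence.

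**The concern.** The main claim has two full-level tests, while the sample size treats it as one. The two can be reconciled only through a success rule, and the article gives none. If a significant result at either time point confirms hypothesis 1, the chance of a false confirmation exceeds 5%. If both are required, the chance of a true confirmation falls below 0.80.

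The choice matters in this trial because the two time points answer different questions. The scheduled telephone calls are in weeks 8 and 12 after rehabilitation, and the Discussion presents the twelve-month follow-up as the source of evidence on long-term effectiveness. An effect at six months that has faded by twelve is plausible. The article does not say whether such a result would confirm the main hypothesis, so that decision could be left until the data are known.

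**Working it through.** **Inputs from the protocol article.** Two-sided 0.05 and power 0.8; 132 per group; difference 360 MET-min per week; loss to follow-up at most 35%; 5% allowance for a non-parametric test; target 370 (all Sample size). 412 patients recruited (abstract and Discussion). Tests at six and twelve months, each at 0.05 (Statistical analysis).

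**Assumption.** The correlation between the two test statistics is not given. A range of 0 to 0.9 is used.

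**1. The plan's own figure.** No standard deviation is stated, so 264 cannot be reproduced independently. Solving backwards with the normal approximation:

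SD = 360 / [√(2/132) × (1.960 + 0.842)] = 360 / 0.345 ≈ 1044 MET-min per week, a standardised difference of about 0.345.

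The target does reproduce: 264 × 1.40 = 369.6, rounded to 370. The sample size is therefore that of one test at 0.05, with no allowance for a second.

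**2. Either time point counts.** With no effect, the chance of at least one significant result is 1 − P(|Z₁| ≤ 1.96 and |Z₂| ≤ 1.96), with Z₁ and Z₂ bivariate normal:

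| Correlation | False-positive rate |
|---|---|
| 0 | 1 − 0.95² = 9.75% |
| 0.5 | 9.1% |
| 0.7 | 8.3% |
| 0.9 | 7.0% |

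**3. Both time points required.** The false-positive rate is then at most 5%. If each test has power 0.80, each statistic has mean 1.960 + 0.842 = 2.80, and joint power is P(Z₁ > 1.96 and Z₂ > 1.96):

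| Correlation | Joint power |
|---|---|
| 0 | 0.80² = 0.64 |
| 0.5 | 0.69 |
| 0.7 | 0.71 |
| 0.9 | 0.75 |

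**4. If fewer patients are lost.** At 35% loss, 412 × 0.65 ≈ 268 remain, close to 264, so step 3 applies. At an assumed loss of 20%, 412 × 0.80 ≈ 330 remain, or 165 per group. The mean of each statistic is 0.345 × √(165/2) ≈ 3.13, and power per test is about 0.88. Taking off the 5% allowance leaves 330/1.05 ≈ 314, or 157 per group, and power of about 0.86. Joint power then runs from 0.86² ≈ 0.74 (power 0.86, correlation 0) to about 0.84 (power 0.88, correlation 0.9).

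**5. Price of splitting the level instead.** At 0.025 per time point the critical value is 2.241. The size per group is 132 × [(2.241 + 0.842)/2.802]² ≈ 160, so 320 evaluable patients instead of 264. With 132 per group, power per test falls to Φ(2.802 − 2.241) ≈ 0.71.

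**The case against.** The strongest reply is that the six- and twelve-month comparisons are two separate claims. One concerns a medium-term effect and the other its persistence. Each then answers its own question at its own 5%, and many statisticians would not adjust. That is a fair reading of the wording of hypothesis 1. It removes the inflation, but it leaves open which of the two is the trial's primary result and which one the 0.80 power describes.

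A second reply is that a journal article condenses the full protocol, and that multiplicity procedures are commonly left to an analysis plan. This holds for the handling of hypotheses 2 and 3. It does not fully cover hypothesis 1, because the article itself puts both time points into the main hypothesis and fixes 0.05 for every analysis. Still, a document that is not shown may settle the matter.

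Three stronger readings may tempt a reader, and the article supports none of them.

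- **Six equal chances at the main claim.** Three hypotheses at two time points make six tests, and a much larger error rate could be computed for them. But the Sample size section ranks hypothesis 1 as the main one, so hypotheses 2 and 3 can be read as supportive. Total activity also contains leisure and transport activity, and the same patients are measured twice, so the tests are not independent. The article gives no correlations from which to compute a realistic figure.
- **A broken promise of 5% overall.** The article sets a threshold per analysis and uses 0.05 in one power calculation. It does not promise a familywise rate.
- **A time point chosen after seeing results.** Nothing shows this. The article only leaves room for it.

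**Conclusion.** The point holds for hypothesis 1. The hypothesis, the analysis rule and the sample size do not fit together until a primary time point and a success rule are stated. If either time point is enough, the false-positive rate for the main claim is about 7% to 9.75%. If both are required, joint power is about 0.64 to 0.75 when each test has exactly 0.80. The second range is not a firm prediction: 412 patients were recruited against a target of 370, and 35% loss is described as a maximum, so power may be better.

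All these figures rest on an assumed correlation of 0 to 0.9 and on normal approximations. The figures for 20% loss and for a split level also rest on the back-calculated standardised difference of 0.345. The ambiguity should be fixed. It does not invalidate the design, and the sample size need not change.

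**What to change.** Name hypothesis 1 at one time point, six or twelve months, as the single primary test at two-sided 0.05, and state that the 0.80 power refers to it. Test hypothesis 1 at the other time point, also at 0.05, only if the first test succeeds. Label hypotheses 2 and 3 as supportive, or place them later in the same sequence. Restrict the general 0.05 rule accordingly.

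Record the choice before any between-group comparison of six-month or twelve-month data. A deadline tied only to the twelve-month analysis would be too late: six-month follow-up was due to be complete in October 2014 and the article appeared on 22 November 2014. If six-month results have already been compared between groups, disclose that alongside the choice.

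The cost is a short paragraph and a dated record. The primary test keeps its level, its power and the 264 evaluable patients. The drawback is that later tests depend on the first: if it fails, a significant result at the other time point is exploratory. Splitting the level would avoid that dependence, but at the price shown above: 320 evaluable patients, or power of about 0.71 per test.

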## Discussion

Low levels of PA in the population require treatment strategies in PA promotion. Therefore, there is a need to develop, evaluate and disseminate approaches that are effective in promoting PA and especially promoting the maintenance of PA. Furthermore, from a Public Health perspective, it is of utmost importance to reach a relevant target group for PA promotion.

Although the study is well-considered, several operational challenges have to be taken into account. One challenge is the recruitment of a sufficient number of patients. During the one-year recruitment, 412 patients could be included in the study. However, recruitment period had to be extended for three months to achieve the target sample size. Second, a selection bias needs to be controlled. Furthermore, the patients’ utilization of the interactive web 2.0 platform as well as target group specific development of the web content seems to be challenging. While planning the study, it is hard to anticipate how to design a motivating web 2.0 platform for CLBP patients after inpatient rehabilitation.

There are several strengths in the design of this study. First, the primary outcome measurement PA will not only be measured subjectively (questionnaires) but also objectively in a subgroup of patients. Second, as far as the authors know, the combination of face-to-face, telephone and internet intervention is new and user experiences of different stakeholders (e.g., patients, providers) can be used in order to improve each approach and/or improve the detailed concept of the comprehensive approach to reach the target group. Third, the 12-month follow-up will result in data about long-term effectiveness of PA promotion in CLBP patients. Furthermore, the examination of associations of PA, subjective prognosis of employment and participation is a promising approach to examine the relative significance of PA in regard of the rehabilitation’s primary objectives according to the ICF model.

CLBP patients seem to be a relevant target group for PA promotion. Based on the results of the current study, modification of Movement Coaching for further indications and target groups is planned.

